## Abstract

**Introduction:**

Colorectal cancer (CRC) is the third most common cancer worldwide in men and women. In the metastasized stage, treatment options and prognosis are limited. To address the high medical need of this patient population, we generated a CD276xCD3 bispecific antibody termed CC-3. CD276 is expressed on CRC cells and on tumor vessels, thereby allowing for a “dual” anticancer effect.

**Methods and analysis:**

This first-in-human clinical study is planned as a prospective multicenter trial, enrolling patients with metastatic CRC after three lines of therapy. During the dose-escalation part, initially, an accelerated titration design with single-patient cohorts is employed. Here, each patient will receive a fixed dose level (starting with 50 µg for the first patient); however, between patients, dose level may be increased by up to 100%, depending on the decision of a safety review committee. Upon occurrence of any adverse events (AEs) grade ≥2, dose-limiting toxicity (DLT), or reaching a dose level of ≥800 µg, the escalation will switch to a standard 3 + 3 dose design. After maximum tolerated dose (MTD) has been determined, defined as no more than one of the six patients experiencing DLT, an additional 14 patients receive CC-3 at the MTD level in the dose-expansion phase. Primary endpoints are incidence and severity of AEs, as well as the best objective response to the treatment according to response evaluation criteria in solid tumors (RECIST) 1.1. Secondary endpoints include overall safety, efficacy, survival, quality of life, and pharmacokinetic investigations.

**Ethics and dissemination:**

The CD276xCD3 study was approved by the Ethics Committee of the Medical Faculty of the Heinrich Heine University Düsseldorf and the Paul-Ehrlich-Institut (P00702). Clinical trial results will be published in peer-reviewed journals. Trial registration numbers: ClinicalTrials.cov Registry (NCT05999396) and EU ClinicalTrials Registry (EU trial number 2022-503084-15-00).

## Introduction

1

Colorectal cancer (CRC) is the third most common cancer entity worldwide in men and women (1). It causes approximately 242,000 deaths per year in Europe (2), mainly due to the dismal 5-year overall survival (OS) rates of approximately 20% or below for metastasized disease (3–5). Particularly for the latter, there is a high medical need for new therapeutic strategies. Present treatment options include combinatorial chemotherapy, kinase inhibitors, and various antibodies (6). However, the latter acts mainly by inhibiting growth factors or angiogenesis, as opposed to directly targeting the tumor cells, with limited benefits only.

Antibodies in different formats have achieved considerable success in cancer therapy. A critical issue for their development is the choice of suitable target molecules, i.e., tumor-associated antigens (TAAs) on cancer cells (7, 8), with their abundance, homogeneity, and stability of expression being of particular importance. Additional expression of a target antigen not only on tumor cells but also on structures critical for tumor growth may yield additional benefit. Such structures that are critical for tumor growth are, for example, extracellular matrix and/or neovasculature. Some TAAs further affect tumor immune surveillance. A prominent example is the programmed death ligand 1/ programmed cell death protein1 (PD-L1/PD-1) signaling pathway, which acts as immune escape mechanism. Blocking this pathway, the so-called immune checkpoint inhibition (ICI) can induce regression even of established tumors, and ICI has become standard treatment in several tumor entities, e.g., melanoma (9) and lung cancer (10). In CRC, however, except for the approximately 15% of patients with microsatellite instability (11, 12), which is a rate that drops to 5% in patients with metastasized disease (13, 14), ICI is not effective (15–18).

Other T-cell recruiting strategies that have recently revolutionized cancer treatment comprise bispecific antibodies (bsAbs), which stimulate the T-cell receptor/CD3 complex with their effector part after binding to their target antigen on tumor cells and the functionally closely related chimeric antigen receptor (CAR) T cells. So far, both bsAbs and CAR T cells are only established in hematologic malignancies but not in solid tumors. This may be largely due to lacking access of immune effector cells to the tumor site (19, 20) and may be overcome by targeting antigens expressed not only by the tumor cells themselves but also by the neovasculature/extracellular matrix. This, in turn, may induce a pro-inflammatory microenvironment, facilitating the influx of effector cells (21, 22).

Efficacy of currently available bsAbs and CAR T cells is additionally hampered by side effects due to unspecific activation of the T cells, resulting in a potentially lethal cytokine release syndrome (CRS) (23, 24). This is due to the employed target antigens frequently being not exclusively expressed not only on malignant but also on healthy cells. Thereby, not only are the patients endangered, but also the application of truly effective doses prevented. Recently, we have developed the PSMAxCD3 bsAb CC-1 in an optimized immunoglobulin G (IgG)–based bsAb format (IgGsc) that displays a prolonged half-life and strictly target-restricted activity with accordingly reduced off-target toxicity (25). CC-1 is currently clinically evaluated in patients with prostate cancer (NCT04104607 and NCT05646550) (26). Recently, the target antigen CD276 (also known as B7-H3) has received large interest due to its broad but rather tumor-restricted expression on cancer cells and neovasculature/microenvironment, including CRC (27, 28). Although this molecule has been shown to have costimulatory effects on T cells in mouse models, it is, meanwhile, considered mainly as inhibitor of human T-cell function, e.g., by suppressing interleukin-2 (IL-2) (27). Preparative work for this clinical trial revealed relevant CD276 expression in all investigated metastatic CRC samples. This prompted us to generate a CD276xCD3 bsAb in our IgGsc format CC-3 that, like CC-1, exhibits an optimal half-life but lacks unspecific T-cell activation while having potent antitumor activity (29) intended for treatment of CRC. Presently widely used targets for CAR T cells and bsAbs in preclinical and early clinical stages of development for CRC treatment are epidermal growth factor receptor (EGFR) and carcinoembryonic antigen (CEA) (19, 30, 31). Compared with these and other immunotherapeutics currently in development, targeting CD276 with CC-3 is expected to

cause fewer side effects due to its optimized bsAb format and choice of TAA, which will allow for the application of effective bsAb doses and accordingly increased efficacy;enable “dual targeting” of tumor cells and neovasculature, which will improve the immune effector cells’ access to CRC tumors, facilitating therapeutic success;be a readily available “off the shelf drug,” eliminating the preparatory work required for CAR T-cell production delaying treatment; andallow for convenient dosing schedules according to its prolonged half-life (32).

In our first-in-human (FIH) study reported here, we plan to evaluate CC-3 in patients with metastatic CRC to determine the overall safety and tolerability, as well as the MTD and first signs of efficacy.

## Methods and analysis

2

### Properties of bsAb CC-3

2.1

The bispecific CD276xCD3 antibody CC-3 is an optimized IgG-like molecule (IgGsc format) with substantially improved serum half-life, especially compared with the prototypical BiTE^®^ bsAb format (29). CC-3 was developed on the basis of extensive preliminary work of our group (33), including the development of the PSMAxCD3 bsAb CC-1 in the same format, which shares with CC-3 the reduced biological risk of side effects (25, 26). *In vitro* and *in vivo* analyses with CC-3 show a favorable toxicity profile, comparable with that of CC-1, of which the target dose has been safely applied in the FIH trial. In addition, *in vivo* data in NSG mice show a highly effective tumor eradication (29).

### Study design

2.2

This open-label, multicenter, FIH phase I dose-escalation and dose-expansion study is designed to define the MTD and recommended phase II dose (RP2D) of CC-3 for a subsequent phase II study. In addition, the aim of the dose-expansion part is to collect first evidence for efficacy of the MTD of CC-3 in adult patients with CRC after the third-line therapy. The study is entitled “First-in-human clinical trial to evaluate the safety, tolerability, and preliminary efficacy of the bispecific CD276xCD3 antibody CC-3 in patients with colorectal cancer“ (short title: “CoRe_CC-3”) and will be conducted within the framework of the German Cancer Consortium (DKTK).

### Study approach

2.3

This FIH study will consist of two parts: a dose-escalation part comprising an accelerated titration phase in which the dose level (DL) is fixed for the individual patient but may increase with each patient by up to 100%, depending on safety considerations judged by an SRC. In case of CC-3–induced adverse events (AEs) ≥grade 2 according to Common Terminology Criteria for Adverse Events (CTCAE) version 5.0, dose-limiting toxicity, reaching a DL of ≥800 µg or SRC decision, this accelerated titration phase will be switched to a standard 3 + 3 dose–escalation design. At this stage, dosing will be split in a priming dose (last DL of the accelerated titration part with no AE ≥2 and no DLT) and a target dose (DL at which the stopping criterion was observed that terminated the accelerated titration part). Three patients will be enrolled in this first cohort. If one of these three develops DLT, then three additional patients will be recruited into the cohort. If two patients develop DLT, then the dose is de-escalated to the last DL considered as safe. If no patient of this cohort experiences DLT, then the next DL will be determined by the SRC and applied to a second cohort. This will again consist of three patients and follow the same DLT considerations as the previous cohort. This will be repeated until MTD is determined, with MTD defined as no more than one of the six patients experiencing DLT. Once the MTD is determined, dosing will be fixed at this level. Then, further patients will be recruited until 20 patients altogether have received CC-3 at the MTD. This dose-expansion part will serve to confirm the RP2D and to detect first signs of clinical efficacy (see also **Figures 1**, **2**).

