**Figure 2 f2:**
[figure not shown]
Dose-escalation part. **(A)** Dosing. First patient (Pat 1) receives 50 µg weekly over 16 weeks. During 3 weeks after first application, dose-limiting toxicity (DLT) will be evaluated and the dose level (DL) for the next patient (Pat 2) will be determined by safety review committee (SRC). Repetition of SRC-guided accelerated dose escalation with following patients until occurrence of DLT, AEs ≥2, or decision of SRC, in patient X (Pat X). Switch to 3 + 3 design with last DL before reaching a criterion (Pat X-1) being used as a priming dose (green frame) for the first application, followed by the DL at which the stopping criterion was observed (Pat X) in subsequent applications. When last patient of each cohort has been observed for 21 days after application of target dose, DLT will be evaluated and the dose level for next cohort of at least three patients is determined by SRC. * up to two additional subjects may be enrolled at each DL; ** up to six additional subjects may be enrolled at each DL; *** SRC may decide to add one additional priming dose, so that target dose is reached at week 3 and DLT evaluation period thus prolonged until end of week 4 (dashed lines). **(B)** Flowchart. If no DLT, AEs grade ≥2, or respective decision of SRC occurs, dose levels may be incremented by up to 100% during accelerated dose titration, enabling a rapid increase up to the maximum target dose after a potential minimum of eight patients. After switching to 3 + 3 design, the number of patients per cohort depends on occurrence of DLT, until maximum tolerated dose (MTD) is reached.

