**Figure 3 f3:**
[figure not shown]
Study schedule. Screening ≤28 days. **(A)** Accelerated titration phase. Dose level in the accelerated titration phase is fixed in each patient and is applied once per week. Dose increase in the next patient can be up to 100% based on safety, PK, and PDK data. For the first application of CC-3 at visit T1V1, patients must be treated as in-patients and followed for safety reasons for at least 48 h Subsequent applications of CC-3 are conducted as in-patient with one overnight stay. If well tolerated and upon medical evaluation, the following doses may be administered in an out-patient setting. In-patient treatment (hospitalization for one night) is feasible and allowed for any subsequent CC-3 treatment. **(B)** Standard titration phase. Dose level at which no AE ≥2 and no DLT was observed during the accelerated titration phase is used as priming dose in the first cohort of enrolled patients (green frame). At T2V1, patients receive DL at which stopping criterion was observed in accelerated titration phase. SRC can decide to introduce an additional second (higher) priming dose (yellow frame) to be applied at T2V1, and dose escalation is conducted at T3V1. For the first application of CC-3 at visit T1V1, patients must be treated as in-patients and followed for safety reasons for at least 48 h Subsequent applications of CC-3 are also conducted as in-patient visits with a single overnight stay. After application of at least three target doses was well tolerated and upon medical evaluation, the following target doses may be administered in an out-patient setting. In-patient treatment (hospitalization for one night) is still feasible and allowed for any subsequent CC-3 treatment. EOT, end of treatment; FU, follow-up; EOS, end of study; S, screening; T, treatment cycle; V, visit.

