#### Dose-escalation part

2.7.1

Initially, dose escalation will be conducted using an accelerated titration design with single-patient cohorts for each DL. Up to two additional subjects may be enrolled at each DL in case more PK, pharmacodynamic (PDK), or safety data are deemed necessary by the SRC. A staggered enrollment design is used for each DL, with a minimum observation period of 72 h between two consecutive subjects’ first doses with the same DL. This is considered sufficient to identify CRS as most critical toxicity. Every patient receives a fixed dose, starting with 50 µg in the first cohort. Subsequent doses are determined by the SRC based on PK, PDK, and safety data obtained with the last DL over an observation period of 21 days, during which DLT evaluation is conducted. This accelerated phase will be replaced by a standard 3 + 3 design in case of

any AE grade ≥2 (except AEs unequivocally due to underlying disease or an extraneous cause);occurrence of DLT;DL ≥800 µg; anddecision of SRC based on PK, PDK, and safety data.

In the standard titration phase of the dose-escalation part, the last DL safely applied prior to termination of the accelerated phase is used as priming dose upon first application, followed by the DL at which the stopping criterion was observed in week two and thereafter. Based on PK, PDK, and safety data, the SRC may decide to introduce an additional intermittent priming dose at week 2, in which case the target dose will be applied at week 3. At least three patients are treated per cohort, following a rule-based 3 + 3 design. Up to a maximum of nine patients per cohort may be enrolled if more PK, PDK, or safety data are deemed necessary by the SRC. After completion of the first cohort’s DLT evaluation period (21 days after application of the target dose to the last patient), the DL for the next cohort will be determined by the SRC. This will be done considering all AEs and DLTs as well as PK, PDK, and safety data. The DL can be increased up to 100% of the previous dose. The priming dose applied in the first cohort will further be given at week 1 of every consecutive cohort, followed by the target dose at week 2 or 3, depending on whether the SRC deemed an intermittent priming dose necessary at week 2 (**Figure 2A**).

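### After a toxicity-free switch decided by the safety review committee, section 2.3 makes the priming dose equal to the target dose, while the Figure 2 legend puts it one level lower

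*Protocol article*

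**What the plan says.** The protocol article defines the priming dose of the 3 + 3 phase in four places.

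- Section 2.3 (Study approach): dosing is split into "a priming dose (last DL of the accelerated titration part with no AE ≥2 and no DLT) and a target dose". The target is the "DL at which the stopping criterion was observed that terminated the accelerated titration part".
- Figure 3 legend, part B: "Dose level at which no AE ≥2 and no DLT was observed during the accelerated titration phase is used as priming dose". This is the same toxicity-based criterion, without the word for the last such level.
- Figure 2 legend, part A: "last DL before reaching a criterion (Pat X-1) being used as a priming dose". The legend lists an SRC decision among the criteria that identify patient X.
- Section 2.7.1 (Dose-escalation part): "the last DL safely applied prior to termination of the accelerated phase is used as priming dose upon first application", followed by the stopping level from week two.

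Two of the switch triggers need no toxicity. Section 2.3 states them as "reaching a DL of ≥800 µg or SRC decision, this accelerated titration phase will be switched to a standard 3 + 3" design, and section 2.7.1 says that the SRC decision may rest on PK, pharmacodynamic and safety data.

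Two further rules bear on the point. An accelerated level may hold more than one patient: "Up to two additional subjects may be enrolled at each DL". And the priming dose persists: "The priming dose applied in the first cohort will further be given at week 1 of every consecutive cohort".

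**The concern.** The rule that fixes the week-1 dose should give one answer for one set of data. For a switch called by the SRC without toxicity, it gives two. Under section 2.3 the first 3 + 3 cohort starts at its target dose with no step-up. Under the Figure 2 legend it starts one level lower.

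The consequence is not confined to that cohort, because section 2.7.1 gives the same priming dose in week 1 of every later cohort. Section 2.9 counts DLTs from the first study drug treatment, so week-1 events enter the count. The choice of reading can therefore affect later DLT tallies, and through them the maximum tolerated dose (MTD) and the regimen carried into expansion. Section 2.7.1 names cytokine release syndrome as the most critical toxicity, so it is not a detail whether the first dose is a step-up.

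**Working it through.** **Inputs.** The dose ladders are those of Table 1 (50, 75, 113, … µg, 50% steps) and Table 2 (50, 100, 200, 400, 800, 1,600, 3,200, 4,000 µg, 100% steps until the last). The patient totals of both examples reproduce: 3×1 + 10×6 = 63 for Table 1 and 4×1 + 3×3 + 6 = 19 for Table 2. Both tables list target doses only, so neither shows which priming level was meant.

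**Method.** Each wording was applied literally to six ways in which the accelerated phase could end. The Figure 3 wording is read as meaning the last such level; it then follows section 2.3 throughout.

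| Case | Target (µg) | Section 2.3 and Figure 3 | Figure 2 | Section 2.7.1 |
|---|---|---|---|---|
| a. Toxicity at 113 µg, one patient per level | 113 | 75 | 75 | 75 |
| b. SRC decision at 113 µg, no toxicity, one patient per level | 113 | 113 | 75 | 113 or 75 |
| c. ≥800 µg reached as in Table 2 (nobody given 800 µg in the accelerated phase) | 800 | 400 | 400 | 400 |
| d. ≥800 µg, if one accelerated-phase patient had received 800 µg without toxicity | 800 | 800 | 400 | 800 or 400 |
| e. Three patients at 75 µg, then toxicity in the only patient at 113 µg | 113 | 75 | 75 | 75 |
| f. Toxicity in the second patient at 113 µg | 113 | 75 | 75 by the dose-level phrase, 113 by the patient label | 75 or 113 |

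**Reading the table.**

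1. Case b is the firm conflict. Level X is free of toxicity, so section 2.3 names it as priming. It is also where the criterion was met, so it is the target. Figure 2 takes the level before X.
2. Section 2.7.1 does not settle case b. On its plain words, the last level given safely before the phase ended is X. Read together with the stopping level that follows it, it can mean the level before X.
3. Case d is the same conflict by another trigger, but it arises only if 800 µg is actually given in the accelerated phase. Table 2 does not show that: its last accelerated cohort is 400 µg and its first standard cohort is 800 µg. The Figure 2 legend does not list the 800 µg threshold, but its dose-level phrase gives 400 µg in both c and d.
4. Case f is a lesser point. The patient label in Figure 2 (X minus 1) points to the stopping level itself, whereas the phrase beside it points to the level below. In section 2.7.1 the answer depends on whether safe application is judged by level or by patient.

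**Size.** With a switch after an uneventful 400 µg patient on the Table 2 ladder, section 2.3 gives 400 then 400 µg and Figure 2 gives 200 then 400 µg: 400/200 = 2. With 50% steps the ratio is 1.5 (112.5/75; Table 1 rounds 112.5 to 113).

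**Reach in that example.** The first standard cohort would have target 400 µg, followed by 800, 1,600, 3,200 and 4,000 µg. With Table 2's cohort sizes (three each, six in the last) this is 3 + 3 + 3 + 3 + 6 = 18 escalation patients who would receive the disputed priming dose. This illustrates reach and is not a forecast.

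**The case against.** The best defence is that context points one way. Section 2.3 says dosing will be split, and a reading in which both parts are equal defeats that sentence. The section also refers the reader to Figure 2, whose legend covers the SRC case. On this view the parenthesis in section 2.3 was simply drafted with a toxicity switch in mind. That is plausible, but it is an inference about intent. The printed criterion says otherwise, and the Figure 3 legend repeats it.

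A second defence is that the SRC reviews all the data, calls this switch itself and can sort the matter out. The article lets the SRC set the next level and add a second priming dose, but it fixes the first priming dose by rule, and the rules conflict. The substantial amendment required before expansion (section 2.7.2) will state the levels applied there. That limits the consequence for expansion patients but comes too late for escalation.

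A third is that an article condenses a fuller protocol. That would answer a complaint about missing detail. Here the printed statements disagree with each other.

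Two stronger readings are tempting, and the document does not support them.

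- A reader might infer that the definitions agree only when every level holds one patient and toxicity triggers the switch. Cases c and e refute this: the ≥800 µg switch in Table 2 involves no toxicity, extra patients at a lower level change nothing, and all wordings agree in both. The multi-patient divergence in Figure 2 rests on the patient label alone.
- A reader might also count every post-switch patient in the worked examples as affected: 3 + 3 + 3 + 6 = 15 in Table 2 and 10×6 = 60 in Table 1. The 15 belong to the ≥800 µg switch, where there is no conflict, and Table 1 names no trigger.

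**Conclusion.** The point holds in a limited form. For an SRC-decided switch without a grade ≥2 adverse event or DLT, section 2.3 and the Figure 3 legend contradict the Figure 2 legend on the priming dose. Section 2.7.1 can be read either way. The readings differ by one dose level: 2-fold at the permitted 100% step and 1.5-fold at 50% steps.

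This rests on two assumptions: that the SRC can end the phase on data other than toxicity, which section 2.7.1 allows, and that the level where the criterion was met is that of the patient just reviewed, as Figure 2 has it. How likely such a switch is cannot be judged from the document.

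It is an inconsistency in a stated rule, not a flaw in the escalation design. It should be corrected because the priming dose persists through all later cohorts and, by section 2.9, lies inside the DLT window. Nothing here says which level is clinically right.

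**What to change.** Reconcile sections 2.3 and 2.7.1 and the legends of Figures 2 and 3 into a single definition of the priming and target levels. It should be indexed by dose level, not by patient number, and should state what applies:

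- for each switch trigger, including an SRC decision without toxicity and a level of ≥800 µg that has actually been given in the accelerated phase;
- when the stopping level holds more than one patient, including whether a level counts as safely applied on the basis of all its patients or of a single one.

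The sponsor and the SRC must decide which level applies in each case. The cost is one paragraph and matching legend edits at the next amendment, with no extra patients or procedures.

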### Justification of starting and target dose

2.4

The definition of the starting dose of 50 µg for CC-3 was based on preclinical data derived from CC-3 dose titrations of *in vitro* T-cell activation and cytokine release, in comparison with pharmacokinetic (PK) data from a clinical study with CC-1 (a bsAb with PSMAxCD3 specificity of otherwise identical format), as well as on clinical experience and clinical studies with MGD009 [a bsAb with CD276xCD3 specificity in a different format (34)] and CD20xCD3 bsAb (35). The maximum dose of 4,000 µg of CC-3 was derived from an *in vivo* model with humanized NOD scid gamma (NSG) mice, in which repetitive dosing with 1.4 µg of CC-3 achieved an eradication of established flank tumors. This dose corresponds to approximately 4,000 µg per week in humans.

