For instance, example 1 (a conservative example) as shown in **Table 1**—(i) a 50% dose increase between cohorts, (ii) one patient treated per cohort in the accelerated titration phase (three cohorts in total), (iii) six patients per cohort in the standard titration phase (10 cohorts in total), (iv) a starting dose of 50 µg, and (v) a maximum tested dose of 4,000 µg—requires a total number of 63 patients in the dose-escalation part.

**Table 1 T1:** Example 1 (a conservative example) of target dose levels in the dose-escalation part.

Level	D1	D2	D3	D3	D4	D5	D6	D7	D8	D9	D10	D11	D12
Cohort	1	2	3	4	5	6	7	8	9	10	11	12	13
Dose (µg)	50	75	113	113*	169	253	380	570	854	1,281	1,922	2,883	4,000
Assumed number of patients per cohort	1	1	1	6	6	6	6	6	6	6	6	6	6
Phase	A	A	A	S	S	S	S	S	S	S	S	S	S

*Standard titration phase is started with new cohorts of initially up to three patients. Treatment schedule is altered to introduce a priming dose on T1V1, leading to application of target dose on T2V1 and consecutive treatment das; A, accelerated titration phase (light gray); S, standard titration phase (dark gray).

Example 2 (a progressive example) as shown in **Table 2**—(i) a 100% dose increase between cohorts, (ii) one patient treated per cohort in the accelerated titration phase (four cohorts in total), (iii) upon a DL of ≥ 800 µg of three additional cohorts with three patients each, (iv) six patients treated in the last cohort of the standard titration phase, (v) a starting dose of 50 µg, and (vi) a maximum tested dose of 4000 µg—requires a total number of 19 patients in the dose-escalation part.

**Table 2 T2:** Example 2 (a progressive example) of target dose levels in the dose-escalation part.

Level	D1	D2	D3	D4	D5	D6	D7	D8
Cohort	1	2	3	4	5	6	7	8
Dose (µg)	50	100	200	400	800	1,600	3,200	4,000
Assumed number of patients per cohort	1	1	1	1	3	3	3	6
Phase	A	A	A	A	S	S	S	S

A, accelerated titration phase (light gray); S, standard titration phase (dark gray).

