In case AE-fulfilling criteria for DLT occur, additional patients are enrolled into the cohort. If two patients experience DLT, then the dose is de-escalated to the previous lower DL that was formerly considered to be safe, and, further, patients receive this lower DL until a total of six patients have been treated or further DLTs develop. If two of the four or two of the six patients experience a DLT, then the DL will be de-escalated to the next lower DL formerly considered to be safe, and patients will receive this lower DL until a total of six patients have been treated (**Figure 2B**). MTD is defined as the DL at which none or one patient experienced a DLT. Once the MTD has been defined, the dose-escalation part of the study is terminated and the dose-expansion part commences.

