#### Dose-expansion part

2.7.2

After the dose-escalation part has been terminated, additional patients are treated until a total of 20 patients have received the DL defined as the MTD. During the dose-expansion part, patients can be treated simultaneously. Prior to the start of the dose-expansion part, a substantial amendment including the applied DLs will be submitted to the regulatory authorities.

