In addition, the implemented one-patient-cohort escalation of CC-3 in the accelerated titration part is considered to benefit the patients included in this trial. Usually, the focus of phase I clinical trials is primarily set on safety and tolerability, and patients enrolled during early phases of a trial frequently do not receive sufficiently effective doses. This problem is addressed in our trial by our approach to rapidly increase CC-3 DLs in order to reach preclinically effective doses already in patients included early in the study. If no DLT is observed, then DL may be increased by up to 100% from one patient to the next, enabling an exponential dosage increment allowing to reach the maximum dose of 4,000 µg already with the 14th patient in case no DLT occur. A dose expansion part will then follow the dose-escalation part to collect first signs of efficacy and define the RP2D.

With the CC-3 antibody showing convincing preclinical activity, we expect that the study will demonstrate a corresponding clinical efficacy regarding objective tumor response and disease control rate, leading to a due benefit for this particular patient population through a trial that is fully funded by public resources.

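### If escalation reaches the 4,000 µg cap with no failed level, the stated rule reports the cap as the MTD although toxicity bounded nothing

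*Protocol article*

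**What the plan says.** Defining the MTD is a stated purpose. The study is "designed to define the MTD and recommended phase II dose (RP2D) of CC-3 for a subsequent phase II study" (Study design, 2.2).

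The MTD is defined twice in the methods:
- Study approach (2.3): "This will be repeated until MTD is determined, with MTD defined as no more than one of the six patients experiencing DLT".
- Dose-escalation part (2.7.1): "MTD is defined as the DL at which none or one patient experienced a DLT".

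The top of the dose range has a different origin. In section 2.4, "The maximum dose of 4,000 µg of CC-3 was derived from an" *in vivo* mouse model in which established tumours were eradicated, and "This dose corresponds to approximately 4,000 µg per week in humans".

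Both worked examples in 2.7.1 escalate through every lower level to 4,000 µg. Example 2 ends with "six patients treated in the last cohort of the standard titration phase", and Table 1 also assumes six patients at that dose. The Discussion describes the path without toxicity, "allowing to reach the maximum dose of 4,000 µg already with the 14th patient in case no DLT occur".

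The Dose-expansion part (2.7.2) gives one dose for expansion: "additional patients are treated until a total of 20 patients have received the DL defined as the MTD".

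**The concern.** A dose can be called the maximum tolerated one only if something above it was not tolerated. Neither definition asks for that; each looks only at the DLT count at the level in question. When the top level is fixed by an efficacy argument and passes, the rule still returns an MTD, and its value is simply the cap.

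Section 2.2 makes the MTD a main result and feeds it into phase II. A reader of the final report would take an MTD of 4,000 µg to mean that higher doses are not tolerated, which the trial would not have tested. Inserting the word *highest* into the definition would not help, because 4,000 µg would be the highest level with at most one DLT and would still qualify.

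**Working it through.** **The article's own counts.** Doubling from 50 µg with a cap gives 50, 100, 200, 400, 800, 1,600, 3,200 and 4,000 µg, as in Table 2. Example 2 needs 4 × 1 + 3 × 3 + 6 = 19 patients, as stated. The first patient at 4,000 µg is number 4 + 9 + 1 = 14, which agrees with the Discussion. Example 1 needs 3 × 1 + 10 × 6 = 63, as stated. So the path to the cap is one the article itself lays out.

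**The rule applied at the cap.** Suppose no level has failed and six patients are evaluated at 4,000 µg.
- With 0/6 or 1/6 DLTs, both definitions are met, so the MTD is 4,000 µg, escalation ends and expansion starts there.
- A drug that causes no DLT at any dose gives this result with certainty.

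This step uses no assumed DLT rate.

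**How often it could happen.** The article gives no DLT rates, so the rates below are assumptions. Write p for the DLT rate and q = 1 − p.
- A level passes 3+3 with 0/3, or with 1/3 followed by 0/3: A = q³ + 3pq² × q³.
- The top cohort of six passes with at most one DLT: T = q⁶ + 6pq⁵.
- Example 2's standard phase has 3+3 at 800, 1,600 and 3,200 µg, then six patients at 4,000 µg: A³ × T.
- Example 1's standard phase has ten cohorts, that is nine levels to pass (here by 3+3) and then the top: A⁹ × T.

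The same rate is assumed at every level, and the accelerated phase is taken to run as in the example.

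| DLT rate p | A | T | Example 2: A³T | Example 1: A⁹T |
|---|---|---|---|---|
| 1% | 0.9988 | 0.9985 | 99.5% | 98.8% |
| 5% | 0.9734 | 0.9672 | 89.2% | 75.9% |
| 10% | 0.9061 | 0.8857 | 65.9% | 36.5% |
| 15% | 0.8138 | 0.7765 | 41.8% | 12.2% |
| 20% | 0.7086 | 0.6554 | 23.3% | 3.0% |
| 33% | 0.4344 | 0.3578 | 2.9% | below 0.1% |

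With rates rising over Example 2's four levels (2%, 5%, 8%, 10%): 0.9954 × 0.9734 × 0.9369 × 0.8857 = 80.4%.

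**What the data at the cap would show.** Exact (Clopper-Pearson) 95% intervals for the DLT rate at 4,000 µg:

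| DLTs / patients | 95% interval |
|---|---|
| 0/6 | 0 to 45.9% |
| 1/6 | 0.4% to 64.1% |
| 0/20 | 0 to 16.8% |
| 1/20 | 0.1% to 24.9% |

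These intervals describe the dose that was tested. None of them says that it is the highest dose that would be tolerated.

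**The case against.** The strongest reply is that only a label is at stake. Expansion at 4,000 µg is reasonable either way, no patient is treated differently, and the recommended phase II dose is named separately from the MTD. This is true, and it limits the severity. It does not remove the point, because the MTD is a declared objective and would be reported as a finding.

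Second, the article is open about the cap: it states the mouse basis and, in both examples, calls 4,000 µg the maximum tested dose. That term appears only as an assumption of the examples. It is not offered as a possible result, and the definitions do not use it.

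Third, the full protocol or the Figure 2B flowchart, which was not available for this check, may contain a branch for the top dose. That is possible. But the article prints an explicit rule, and followed as printed the rule gives the wrong name. The safety board review after the standard phase and the amendment before expansion are real checkpoints. As described, the amendment covers the dose levels to be applied, and neither checkpoint changes the definition.

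Fourth, the probabilities depend on assumed rates and on the shorter example. This stands: on Example 1's path, or with rates of 20% or more, the ending is much less likely. The table shows both paths for that reason.

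**Conclusion.** The concern holds. As written, 0 or 1 DLT in six patients at an efficacy-based cap is declared the MTD, whether or not any dose was shown to be too toxic. That conclusion rests on the wording of sections 2.3, 2.4, 2.7.1 and 2.7.2 alone.

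Its likelihood rests on assumptions. For a drug with low toxicity it is the most likely ending (about 89% on Example 2's path and 76% on Example 1's at a flat 5% rate). For a drug with a DLT rate of 20% or more it is uncommon. Patient safety and the conduct of the trial are not affected. The harm is a headline result that claims more than the trial can show, so the change should be made, but it is not critical.

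**What to change.** Add one rule to sections 2.3, 2.7.1 and 2.7.2:

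- If 4,000 µg is reached and no level has failed, escalation stops once six patients have been evaluated there.
- If at most one of the six has a DLT, the result is reported as *MTD not reached; maximum tested dose 4,000 µg*, with the DLT rate and its exact interval at six patients, updated at 20.
- Expansion and the recommended phase II dose are written as the MTD or, if it is not reached, the maximum tested dose.

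The cost is wording in three sections and a slightly weaker stated conclusion. Doses, cohorts and sample size stay as they are.
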